#### 3.2 Genomics

DNA samples will be obtained from EDTA blood collected from all healthy individuals. After isolation, DNA samples will be sequenced and genetic variations (SNPs) will be determined by a whole-genome SNP array from Illumina (collaboration group Prof. [name], UMC Groningen).

### **3.3 Epigenomics, transcriptomics and metabolomics**

ChIP-PCR analysis will be used to measure enrichment of H3K4me3 and H3K9me3 at the promoter of *TNFA*, *IL6* and *IL1B* in human monocytes isolated from subjects before and after (2 weeks and 3 months) BCG vaccination. Epigenetic changes in monocytes as well as changes in mRNA and metabolites will be measured in all blood samples before and after vaccination.

### **3.4 Microbiome analysis**

Volunteers will be asked to collect gut, oral and vaginal microbiome samples before BCG vaccination and two weeks and 3 months after vaccination. Microbiome analysis will be performed using shotgun sequencing metagenomics. All samples will be stored at -80°C until analysis.

### **3.5 Questionnaires**

At all time points of blood collection, participants are asked to complete a questionnaire addressing questions on: current or previous infections (flu, fever, cold), substance abuse, perceived physical stress, medication (NSAIDs, aspirin), vaccination history (e.g. flu vaccine) etcetera.

Vaccinations will be performed at the outpatient clinic of the Department of Internal Medicine Radboudumc, and the experimental studies will all be performed at the laboratory of Experimental Internal Medicine at the Radboudumc.

## 4. STUDY POPULATION

### 4.1 Population (base)

Healthy volunteers ( $\geq 18$  years old) of Western European ethnic background will be actively recruited using flyers and posters. The gender distribution of the cohort should be around 50% males and 50% females.

### 4.2 Inclusion criteria

In order to be eligible to participate in this study, a subject must meet all of the following criteria:

- Age  $\geq 18$  years
- No known chronic diseases, no acute infection at the time of vaccination
- Written informed consent

### 4.3 Exclusion criteria

A potential subject who meets any of the following criteria will be excluded from participation in this study:

- Use of chronic or acute medication during the last month before the study other than oral anti-contraceptive drugs
- Vaccination within 3 months prior to study period (subjects cannot be vaccinated with other vaccines during the study)
- Medical history of disease associated with immune deficiency
- Previous BCG vaccination
- Contact with tuberculosis patients or born in a tuberculosis endemic country
- Acute (febrile) illness within 4 weeks prior to start of study
- Pregnancy

### 4.4 Sample size calculation

The sample size calculation is not possible due to the variable frequencies of various traits in this study, such as SNP frequency and the variable prevalence of the microorganism classes in the microbiome. The size calculation will be variable depending on which type of polymorphism will be analyzed. The frequencies are not known and therefore power calculations are not possible to perform. Because our aim is to find new DNA polymorphisms that modulate training we need a larger sample size than the *in vivo* BCG studies that have been performed to date. To be able to detect any potential relevant SNPs, we decided to include 300 individuals, based on previous studies within the Human Functional Genomics Project.

## **5. VACCINATION OF SUBJECTS**

### **5.1 Investigational product/treatment**

Subjects in this study will be vaccinated with BCG vaccine (InterVax, Canada) using the standard vaccination technique for this vaccine, which is intradermal injection in the left upper arm. This vaccine is distributed by the Rijksinstituut voor Volksgezondheid en Milieu (RIVM) under approval of the Ministry of VWS and meets the requirements of WHO for dried BCG vaccine.

### **5.2 Use of co-intervention**

Subjects are not allowed to use any medication; an exception is made for oral contraception.

## 6. INVESTIGATIONAL PRODUCT

### 6.1 Name and description of investigational product

Bacille Calmette-Guérin is a live attenuated strain of *Mycobacterium bovis* developed in 1921 to prevent tuberculosis and other mycobacterial related infections. It is the most widely administered vaccine in the world and up to three billion individuals have received the vaccine. BCG is mainly used in countries with a high prevalence of tuberculosis to prevent childhood tuberculous meningitis and miliary disease. Although the vaccine primarily protects against tuberculosis, the vaccine is also effective for protection against leprosy and diseases related to nontuberculous mycobacteria. The BCG vaccine used in this study has been selected by the RIVM for use in the Netherlands (under approval of the Ministry of VWS) and is delivered by InterVax (Toronto, Canada) to the RIVM. The vaccine is registered in Bulgaria and produced by BulBio National Center of Infectious and Parasitic Diseases, BB-NCIPD Ltd. (Sofia, Bulgaria). The vaccine meets all the requirements of WHO for dried BCG vaccine (Requirements for Biological Substances No 11, formulated by WHO Expert Committee of Biological Standardization, Technical Report Series, No 745, 1987; 771, 1988). Package contains 1 ampoule of lyophilized powder (0.5 mg) and 1 ampoule of diluent (1 ml, 0.9% NaCl). After resuspension of lyophilized vaccine in diluent, the vial contains 0.5 mg/ml. According to standard vaccination practices, participants will be vaccinated with 0.1 ml of injection suspension.

### 6.2 Summary of findings from non-clinical studies

*In vitro* experiments with isolated monocytes have demonstrated that BCG is able to induce innate immune memory. If monocytes are incubated with BCG for 24 hours and stimulated 7 days later with unrelated fungal and bacterial pathogens, this will result in a twofold enhanced release of monocyte-derived cytokines, such as IL-6, TNF- $\alpha$  and IL-1 $\beta$ , when compared to non-BCG trained cells. The ability to train monocytes is induced through the NOD2 receptor and mediated by epigenetic reprogramming (Kleinnijenhuis et al., 2012).

### 6.3 Summary of findings from clinical studies

BCG vaccine is the most used human vaccine in the world, with an excellent track record of safety. It mainly protects against severe forms of tuberculosis (meningitis, miliary TB), while providing only a limited protection against pulmonary TB. In addition, epidemiological studies have demonstrated that BCG vaccination reduces infant mortality independent of its effect on tuberculosis, which suggests that BCG might provide nonspecific protection against unrelated infections (Shann, 2013). *In vivo* studies with BCG vaccine performed by our research group have shown that BCG induces training of the innate immune system. The enhanced function of human monocytes persists for at least 3 months after vaccination, some of the protective effects have even been shown to last up to 1 year (Kleinnijenhuis et al., 2012).

#### **6.4 Summary of known and potential risks and benefits**

Apart from protection against extrapulmonary infection with *Mycobacterium tuberculosis* and *Mycobacterium leprae*, there are no expected benefits for participants in the study.

Potential risks include only the side effects of the vaccine, of which localized skin reactions are most common. The local reaction after BCG vaccination is usually mild and self-limiting. Less common are fever and headache after vaccination and if they occur they are typically mild. Enlargement of the axillary lymph nodes may occasionally occur after vaccination but will usually regress spontaneously after a few months.

After vaccination, seroconversion to Mantoux testing has been described to occur in 41.8% of the individuals, which decreases to 21.2% after 10 years (Farhat, Greenaway, Pai, & Menzies, 2006). For these reasons Mantoux testing cannot be used as a diagnostic test for tuberculosis in the future. However, other diagnostic tools are available such as the Quantiferon test and chest X-ray.

Local haematoma formation could occur at the site of vena puncture. See also the summary of product characteristics for a list of side effects.

#### **6.5 Description and justification of route of administration and dosage**

Reconstituted BCG vaccine should be given intradermally. According to standard vaccination practices, the dose for adults is 0.1 ml (see summary of product characteristics).

#### **6.6 Dosages, dosage modifications and method of administration**

0.1 ml of reconstituted BCG vaccine containing 0.050 mg of BCG will be administered intradermally in the left upper arm as recommended by the manufacturer (see summary of product characteristics).

#### **6.7 Preparation and labelling of Investigational Medicinal Product**

BCG vaccine will be purchased from the Clinical Pharmacy of the Radboudumc. Vaccines will be labeled according to GMP. Storage and preparation of vaccines will be done by experienced researchers.

#### **6.8 Drug accountability**

BCG vaccine will be purchased from the Clinical Pharmacy of the Radboudumc. Vaccines will be stored at 4°C in a room with temperature registration through the Xiltrix system. Vaccines will be kept in a dedicated box, labeled according to GMP. No other medication will be kept here. Issue of vaccines will be monitored on a drug accountability sheet.

## 7. METHODS

### 7.1 Study parameters/endpoints

#### 7.1.1 Main study parameter/endpoint

According to the objectives:

##### **1) Assessment of immune cell function**

###### **a. Stimulation Assays**

Before BCG vaccination and at two different time points after vaccination (2 weeks and 3 months) blood will be drawn from which monocytes will be isolated by density centrifugation over Ficoll-Paque.

Cells will be restimulated *ex vivo* with different stimuli:

- control culture medium (RPMI)
- *E. coli* LPS (10ng/ml)
- *M. tuberculosis*  $1 \times 10^6$  microorganisms/ml
- *C. albicans*  $1 \times 10^6$  microorganisms/ml
- *S. aureus*  $1 \times 10^6$  microorganisms/ml

###### **b. Cytokine Measurements**

Cytokine production will be assessed with ELISA after 24h (IL-6, TNF $\alpha$ , IL1- $\beta$ ) or 7 days (IFN $\gamma$ , IL-17, IL-22) incubation. The cytokine production at two different time points after vaccination will be compared with the response before vaccination.

###### **c. Immunophenotyping**

Immunophenotyping of cell subpopulations using myeloid cell and lymphocyte protocols will be done using FACS analysis.

##### **2) Genomics**

Genetic variation will be assessed by a genome-wide SNP array from Illumina.

##### **3) Epigenomics, transcriptomics, metabolomics**

Epigenetic changes by ChIP-PCR as well as differences in transcriptome (by RNA sequencing) and metabolome (perform at Metabolon) will be determined before and after vaccination.

##### **4) Microbiome**

Human microbiome variation will be measured by shotgun metagenomics in collaboration with the group of [name] (Broad Institute/MIT).

#### 7.1.2 Other study parameters

##### **5) Metadata**

Metadata (clinical, environmental data) will be collected from all subjects using questionnaires at each visit.

## **6) Skin inflammation at vaccination site**

The vaccination site will be examined two weeks after BCG vaccination. A picture will be taken and scar size and the presence of local inflammation will be documented by an independent researcher.

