### Secondary objectives:

6. Investigate whether environmental factors such as diet, psychological stress and season influence the ability to induce adaptive immunity and trained immunity by BCG vaccination.
7. Investigate if local skin inflammation and development of vaccination scar at the vaccination site 2 weeks after BCG vaccination correlate with induction of trained immunity.
8. Investigate whether the capacity of monocytes to display trained immunity in *in vitro* experiments correlates with trained immunity *in vivo*.

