## 9. STATISTICAL ANALYSIS

### 9.1 Primary study parameter(s)

The first step in the analysis of this study will be to examine the induction of adaptive immune memory and trained immunity in the cohort and to determine the variation between subjects. Inter-individual variation of the cytokine responses will be evaluated using Fligner-Killeen test of homogeneity of variances. The variance for each of the stimulation conditions will be compared to the unstimulated state.

Cytokine production upon *ex vivo* restimulation of monocytes before vaccination will be compared with cytokine levels after vaccination with BCG. Since every subject will be compared to themselves and cytokine production is considered to be non-parametric, the Wilcoxon signed rank test will be used in order to calculate the enhanced function of monocytes (trained immunity).

Results will be expressed as means  $\pm$  standard errors of the means (SEM). P values less than 0,05 are considered statistically significant.

All tests will be performed on GraphPad Prism 6.0 software (GraphPad).

To determine and link genetic polymorphisms to trained immunity, genotype data will be analyzed using haploview software. The Wilcoxon signed rank test will be used in metabolomics and epigenomics studies in order to compare data before and after vaccination. Data validation will be essential to ensure that findings are not false positives.

Microbiome reads will be first processed using KneadData. This includes quality-trimming (trimmomatic parameters: MAXINFO:90:0.5), read-filtering based on a minimum read length of 60bp and removal of potential human contamination by filtering reads that aligned to the human genome (reference genome hg19). Quality-controlled, paired-end reads will be aligned against a database of unique clade-specific marker genes using bowtie2 and taxonomic profiles and inferred with MetaPhlAn 2.2 (Segata et al., 2012). For the subsequent analysis we will consider species as well as genus composition of the samples. Functional microbiome profiling will be done using HUMAnN2 (Segata et al., 2013). Briefly, reads will be mapped against a customized database of functionally annotated pangenomes only considering organisms that were identified during the taxonomic profiling step. Functional annotation of the protein-sequences in the pangenomes to their respective UniRef50 family will be provided.

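### Local inflammation is documented only as presence, although secondary objective 7 asks whether it correlates with trained immunity; no size or grade is fixed

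*Protocol*

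**What the plan says.** Protocol section 2, secondary objective 7, is to investigate whether "local skin inflammation and development of vaccination scar at the vaccination site 2 weeks after BCG vaccination correlate with induction of trained immunity". Inflammation and scar are listed as two separate variables.

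The measurement is defined in section 7.1.2, item 6. There is one reading: "The vaccination site will be examined two weeks after BCG vaccination". A photograph is taken, and "scar size and the presence of local inflammation will be documented by an independent researcher". No diameter, grade or score for inflammation appears anywhere in the protocol, and no grading of the photograph is planned.

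On how often volunteers react, section 6.4 says only that among the side effects "localized skin reactions are most common" and that "The local reaction after BCG vaccination is usually mild and self-limiting". Section 10.3 repeats this. No percentage is given for visible inflammation at two weeks.

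On size, section 4.4 says "we decided to include 300 individuals, based on previous studies within the Human Functional Genomics Project", without a power calculation. Section 9.1 sets the threshold: "P values less than 0,05 are considered statistically significant".

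**The concern.** The study sets out to explain why the size of the response to BCG differs between people. For the skin reaction that calls for a variable that orders volunteers by strength. Presence puts a faint redness and a large indurated lesion in the same class, so differences among reactors are lost at the point of recording. A later analysis plan cannot restore a measurement that was not taken at the visit.

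What is at stake is the inflammation half of objective 7: a real but weak association between strength of reaction and training could be missed.

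**Working it through.** The protocol states no power, prevalence or effect size for this objective, so there is no figure of its own to reproduce. What follows is a sensitivity check.

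**Inputs from the protocol:** n = 300 (section 4.4); significance level 0.05 (section 9.1).

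**Assumptions:** two-sided test; all 300 volunteers evaluable; a single continuous measure of training; a normally distributed underlying reaction strength; true correlation r = 0.20; share p scored present varied from 50% to 95%.

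**Step 1, information kept by a yes/no record.** The relative efficiency of cutting a normal variable at prevalence p is E = φ(z_p)² / [p(1 − p)]. At p = 0.5, φ(0) = 0.399 and E = 0.159/0.25 = 0.64. At p = 0.8, φ(0.842) = 0.280 and E = 0.0784/0.16 = 0.49. The formula is symmetric, so 20% present gives the same value as 80%.

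**Step 2, power.** The correlation shrinks to r√E. By Fisher's z, power = Φ(atanh(r√E)·√297 − 1.96). For a fully graded measure E = 1, which gives Φ(0.2027 × 17.23 − 1.96) = Φ(1.53) = 94%.

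| Share present | E | Worth, of 300 | √E | Power, r = 0.20 | Smallest r at 80% power |
|---|---|---|---|---|---|
| fully graded | 1 | 300 | 1 | 94% | 0.16 |
| 50% | 0.64 | 191 | 0.80 | 79% | 0.20 |
| 80% or 20% | 0.49 | 147 | 0.70 | 68% | 0.23 |
| 90% or 10% | 0.34 | 103 | 0.59 | 53% | 0.28 |
| 95% or 5% | 0.22 | 67 | 0.47 | 37% | 0.34 |

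The last column is 0.161/√E, where 0.161 = tanh[(1.96 + 0.84)/17.23].

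**Step 3, a stronger association.** At a true r of 0.3 the yes/no record still has 99%, 96%, 86% and 69% power at 50%, 80%, 90% and 95% present.

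**Step 4, what a diameter could recover.** Volunteers without a reaction all read 0, so a diameter is not fully graded either. Take Y = max(0, Z + c), with Z standard normal and Φ(c) = p. Its correlation with Z is p/SD(Y), where E[Y] = cp + φ(c) and E[Y²] = (c² + 1)p + cφ(c).

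- p = 0.8: variance 1.602 − 0.953² = 0.694, correlation 0.8/0.833 = 0.96, power at r = 0.20 about 92% (yes/no 68%).
- p = 0.5: variance 0.5 − 0.399² = 0.341, correlation 0.5/0.584 = 0.86, power about 85% (yes/no 79%).
- p = 0.2: variance 0.106 − 0.112² = 0.094, correlation 0.2/0.306 = 0.65, power about 62% (yes/no 68%).

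The diameter helps clearly when half or more of the volunteers react. When few react it adds nothing in a linear correlation.

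**The case against.** Four objections deserve weight.

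- *The wording does not say yes/no.* Documenting presence does not exclude a grade on the form, and scoring detail is often left to other documents. This stands in part. But the same sentence fixes a size for the scar and none for inflammation, so presence is the only rule the protocol gives, and it governs what is collected.
- *Some variation is kept elsewhere.* Scar size is graded and every site is photographed. This also stands in part. Scar is a separate variable in objective 7, and a photograph could be graded for redness later. No such grading or scale reference is planned, however, and induration cannot be read from a picture.
- *The protocol does not imply that nearly everyone is positive.* A reader might infer from section 6.4 that almost all volunteers will be scored present, so that the item sits at its ceiling and can hardly correlate with anything. The text does not support that. It ranks local reactions above fever and headache; it gives no frequency and says nothing about two weeks. A mild, self-limiting reaction may equally have faded in some volunteers by then.
- *Moderate associations survive.* This stands in full. At r = 0.3 power is still 86% with 90% present (step 3), so a null result is not the expected outcome.

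**Conclusion.** The concern holds in a limited form. For inflammation the protocol fixes presence alone, while objective 7 needs a variable that reflects strength of reaction. Some information is lost at any prevalence: at least 36% under a normal underlying reaction, 51% at 80% or 20% present, and 78% at 95% or 5%. A weak association (r = 0.20) could be missed.

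How large the loss is rests on the normal model and on a two-week prevalence that the protocol does not give. Neither a ceiling nor a predicted null finding is shown. The matter affects one half of one secondary objective, listed among the other study parameters, and no primary question depends on it. It is minor: a cheap improvement in measurement that has to be made before the visits take place.

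**What to change.** Amend section 7.1.2, item 6, and the recording form so that at the existing two-week examination the same independent researcher records the widest diameter of redness and of induration in mm, entering 0 if there is none. Place a ruler in the photograph that is already taken.

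State in advance which diameter is the inflammation variable for objective 7, so that two readings do not become two tests. Derive presence from the diameters, so that the yes/no comparison stays available if few volunteers react.

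The cost is about one minute and two extra form fields per volunteer, or roughly five hours over 300 volunteers (300 × 1 minute). It needs no extra visit, blood draw or assessor.

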## **7.2 Study procedures**

All experiments and handling of samples will be done according to GCP standards. Subjects will be actively recruited using flyers and posters. If they meet the in- and exclusion criteria they will be informed about the study by the investigator and they will receive documentation regarding the study. A pregnancy test will be performed for female volunteers. If volunteers that meet all inclusion and exclusion criteria want to participate in the study, informed consent is signed. A Mantoux test will not be part of the procedure since 1) participants from tuberculosis endemic countries are excluded from the studies, and 2) a Mantoux test itself could potentially influence the effects induced by BCG.

### **Invasive procedures to be performed:**

Day 0 (visit 1): vena puncture: 2.5 ml PaxGene tube, 50 ml EDTA blood, 8 ml serum  
vaccination with BCG vaccine.

Day 14 (visit 2): vena puncture: 2.5 ml PaxGene tube, 50 ml EDTA blood, 8 ml serum

Month 3 (visit 3): vena puncture: 2.5 ml PaxGene tube, 50 ml EDTA blood, 8 ml serum

### **Other procedures regarding subjects:**

#### **1) Questionnaires**

At all time points metadata will be collected using questionnaires. At the first visit this will be a more extensive list of questions regarding lifestyle, that will take about 20 minutes to complete. At all other time points the questionnaire will be shorter and will take about 5 minutes to complete. It addresses questions on current health status, level of physical stress etcetera (see the F1 questionnaire document for a complete overview).

#### **2) Microbiome**

Stool, oral and vaginal samples will be collected by the participants in three separate containers on day 0, day 14 and 3 months after vaccination.

### **Laboratory techniques to be performed:**

**Stimulation and cytokine assays:** At all time points PBMC isolation will be performed and monocytes will be *ex vivo* stimulated with various pathogens. Cytokine production will be assessed after 24 hours and after 7 days with ELISA technique. Cytokine levels before and after vaccination will be compared. Immunophenotyping will be done using FACS analysis.

**Genomics:** At the first visit 3 ml of blood for DNA isolation of healthy volunteers will be stored.

**Microbiome:** Samples will be analysed by shotgun metagenome sequencing.

**Epigenomics, transcriptomics metabolomics:** Supernatant and cell lysates will be stored for epigenomics, transcriptomics and metabolomics studies.

